**Table 2 Tab2:**
[figure not shown]
Timetable of the prospective stepped-wedge randomized controlled trial. The trial will terminate in 26 months from its initiation

Blue: Observation phase (months 1–8 or more)

Yellow: Intervention phase (months 9–26)

Green: Post-rollout period (maternal feedback by telephone of the last questionnaires, months 27–28)

**Fig. 2 Fig2:**
[figure not shown]
Schedule of enrolment, interventions, and assessments for ENGAGE trial

### Interventions

The 18-month interventions will include a presentation of the HSOG Guidelines, case discussions focusing on guidelines application, training workshops for evidence-based best practices, use of a purpose-built website, educational reminders, and auditing and feedback on the utilization rates [31, 32]. There will be intervention at all the different levels of unit clinical practice: director, obstetricians, trainees in obstetrics, and midwives. Table 3 summarizes the components of the study’s intervention.

**Table 3 Tab3:** Components of study’s intervention

**Local opinion leaders**
-Departmental chair and/or obstetrician nominated by departmental chair
**Electronic files sent to the participants** -PDF info and video: use of REDCap platform, presentation of study’s questionnaires, communicating study’s objectives (at the start of the observation period)
**Interactive webinars, courses, and workshops** -All staff involved in deliveries and collaborating with the participating obstetricians will join the following workshops: A. 2-day course, just prior to the intervention period. This course will be repeated 2–3 times for each unit during the intervention period. • Day 1 – Part 1: Theory - presentations and interactive discussion: - ENGAGE study interventions - HSOG Guideline on cesarean section and VBAC - HSOG Guideline on induction and augmentation of labor - Robson cesarean sections classification - Organization of labor ward - Obstetric emergencies - Medicolegal issues in cesarean sections • Day 1 – Part 2: Video demonstrations - Breech delivery - Twins delivery - External cephalic version - Delivery of other abnormal presentations - Forceps - VBAC - Fetal blood sampling • Day 2: Cardiotocography (CTG) physiological interpretation course (accurate evaluation of fetal distress and avoidance of unnecessary interventions) B. 1-day hands-on workshop on site: - Breech delivery - Twins delivery - External cephalic version - Delivery of other abnormal presentations - Forceps - VBAC C. 1-day meetings (recurring once or twice monthly): cesarean section and CTG online meetings with review of patient notes (duration 60 min)
**Detailing** -Advice to overcome barriers of different categories -Discussion with participating obstetricians and supporting staff during the intervention period about organization issues and adaptation to changes
**Instruction on achieving compliance with best practices** -Training within courses and meeting or teleconference with members of the steering committee when issues arise
**Compliance enhancement** -Regular meetings locally (cardiotocography meeting, cesarean section meeting, once or twice monthly, during the intervention period) -Follow-up meetings with study’s facilitators (physical presence, teleconferences every 2–4 weeks, phone calls) about the above topics or others which may arise -A dedicated person (member of study’s staff) will visit each unit every 3 months. During the visit she/he will accommodate data acquisition and local participating obstetricians’ familiarity with the study’s platform and serve the study’s board activities indicated locally.
**Reminders of good obstetric practice** -Placing reminders for enhancement of vaginal birth in labor wards. Placing posters in staff rooms and above theater hand wash basins. - Mobile phone short text messages - Newsletter messages sent on a weekly basis during the intervention period
**Audit and feedback** -Regular email reports of departmental performance. Live real-time statistics will be available for each participating department on the REDCap platform.
**Information technology** A website has been developed (www.emgetrial.gr) for the participating obstetricians and staff to access the guidelines and download evidence-based information (plus other information, e.g., Robson criteria for cesarean sections).

Various types of intervention will be provided:The establishment in daily practice of three guidelines and two consent forms that were published by the HSOG. The titles of the guidelines and the consent forms are depicted in Table 4. Realizing the crucial need to apply evidence-based medicine in obstetrics, HSOG has published these guidelines and consent forms based on international guidelines. All of them were posted and made freely available for comments on the HSOG website (www.hsog.gr) for at least one month. Following this, further feedback was provided by the HSOG’s Scientific Committee, subsequent to which the guidelines were approved by the Society’s Board for final publication. The same procedure was followed for the two consent forms. The guidelines and consent forms are written in Greek and are freely available in PDF format through the Society’s website. The principal investigator and the local trial investigator discuss and disseminate the guidelines among the participating staff at the respective units, providing the opportunity to identify specific barriers of their practice. This requirement was instituted so that the planned activities could be adapted in such a way as to overcome them as well as to draw up an implementation timetable [33].At least one session with the physical presence of the Principal Investigator, the trial coordinators, and the staff will take place shortly before they switch on the intervention period in each participating unit so that the local obstetricians and midwives may be informed on the objectives and interventions of the study. Prior to this, correspondence by email will provide details, such as the trial questionnaires and other required paperwork.All staff, including midwives and trainee doctors, involved in the participating units will receive a PDF document and a video just prior to the study initiation. These explain the use of the purpose-built electronic platform (REDCap) and how to fill the study’s questionnaires.All staff, including midwives and trainee doctors, involved in deliveries and collaborating with participating obstetricians will participate in interactive courses and workshops immediately prior to the intervention period of the study. There will also be a 2-day online course just prior the intervention period. The 1^st^ day’s schedule will include presentations and interactive discussion on such topics as ENGAGE study interventions, the HSOG Guideline on cesarean section and VBAC, the HSOG Guideline on induction and augmentation of labor, Robson cesarean sections classification, organization of the labor ward, obstetric emergencies, medicolegal issues on cesarean section, and video demonstrations of several cases such as breech delivery, twins delivery, external cephalic version, delivery of other abnormal presentations, instrumental delivery, VBAC, and fetal blood sampling. The duration of the 1^st^ day of the course is estimated at approximately 8 h. The 2^nd^ day’s schedule will be mainly devoted to a cardiotocography (CTG) physiological interpretation course (evaluation of fetal distress and avoidance of unnecessary interventions). The duration of the 2^nd^ day of the course is estimated at approximately 6 h.

**Table 4 Tab4:** HSOG Guidelines and Consent Forms included at the intervention phase (www.hsog.gr)

**Guideline or consent form**	**Title**
Guideline 1	Labor induction
Guideline 2	Cesarean section
Guideline 3	Vaginal birth after cesarean section
Consent form 1	Cesarean section
Consent form 1	Cesarean section for placenta praevia

A hands-on workshop using mannequins will also take place on-site for each unit prior to initiation of the intervention period during the scheduled visit of the members of the Committees and staff: it will include several workstations, such as breech delivery, twins delivery, external cephalic version, delivery of other abnormal presentations, forceps delivery, and VBAC. Participants will have the opportunity to practice what was taught during the previous 2-day theoretical course in a setting simulating real-life conditions. The duration of this activity is estimated at 2–3 h, depending on the number of participants from each unit.

An online cesarean section and CTG meeting with a review of the patient notes will take place once or twice monthly with participants from the units, who will at that same point of time be at the intervention phase of the study.

The online courses and hands-on workshops will be given on consecutive days and will be conducted by experienced trainers. Training groups will be limited to only the participating professionals each time in order to ensure adequate training. The purpose of this activity is to make clear the study’s objectives, which are to focus on the need for evidence-based clinical practice and to review the HSOG Guidelines on labor induction, cesarean section, and vaginal birth after cesarean section, along with HSOG’s consent forms. Another crucial aim is to pinpoint what are the barriers to the use of these guidelines in the participating obstetric departments, overcome these barriers, and eventually implement the guidelines.5.Throughout the intervention period, compliance with guidelines will be enhanced by regular follow-up meetings with the Principal Investigator, members of the committees, and local principal investigators or opinion leaders participating in the study, via either physical presence, teleconferences, or phone calls. Feedback will also be adjusted independently based on locally preferred routes of better tailoring the intervention to the unit’s daily practice. Additional visits may follow if deemed necessary based on platform statistics.6.A member of the study’s staff will visit each unit every 3 months. During the visit, she/he will accommodate data acquisition and local participating obstetricians’ familiarity with the study’s platform while also serving the study committees’ actions indicated locally. A number of at least four visits per participating unit is estimated.7.Use of the Robson 10-group classification criteria embedded in the electronic questionnaire (Table 5) and written feedback on the unit’s cesarean section rates on a regular basis will identify the higher categories that should and may be reduced further.8.Live real-time statistics will be provided, as demanded by the unit basis, to enable the participating units to see their performance. This type of feedback is expected to improve adherence to the interventions.9.Cesarean section and CTG interpretation meetings will be held once to twice monthly during which cesarean sections and “abnormal” CTG cases will be discussed. Participants will be the units that are at the intervention phase of the study precisely when the meeting takes place. The members of steering committee and local contributors to the study may actively participate in these meetings by physical presence, teleconference, or phone call. This is expected to further enhance compliance.10.Reminders about good obstetric practice will be placed in labor wards, staff rooms, and above theater hand wash basins. These will be short printed messages on the importance of improving the rate of vaginal birth offering birth attendants hints to reduce cesarean section rates. The reminder-texts will be planned in accordance with preferred recommendations, carefully considering the defining features and the barriers to the adoption of evidence-based birth practices and to the use of the guidelines in Greece. These reminders will also be sent to the participants by newsletters and mobile sms. Every week they will receive a different reminder. When the existing reminders come to an end, a restatement of the reminders will follow again by newsletter.

**Table 5 Tab5:** The 10 groups of the Robson Classification used in the ENGAGE Trial (World Health Organization implementation manual)

**Robson classification**	
1	Nulliparous, single cephalic, ≥ 37 weeks, in spontaneous labor
2	Nulliparous, single cephalic, ≥ 37 weeks, induced or cesarean section before labor
3	Multiparous (excluding previous cesarean section), single cephalic, ≥ 37 weeks, in spontaneous labor
4	Multiparous (excluding previous cesarean section), single cephalic, ≥ 37 weeks, induced or cesarean section before labor
5	Previous cesarean section, single cephalic, ≥ 37 weeks
6	All nulliparous breeches
7	All multiparous breeches (including previous cesarean section)
8	All multiple pregnancies (including previous cesarean section)
9	All abnormal lies (including previous cesarean section)
10	All single cephalic, < 37 weeks (including previous cesarean section)

This type of study was chosen as the optimal method to examine the effects of a new intervention applied in several population groups and analyzing/measuring the performance of the intervention for each unit’s population individually and as a whole. As already mentioned, the intervention study is characterized by a random sequel from the observation status to the intervention mode in different time intervals (every month) for each two of the participating units. This will create informative data at each step for both the observation and intervention periods.

### Randomization

The Greek territory has been divided into six geographic divisions based on location. Each of the participating departments will be randomly assigned per stratum to the 11 intervention steps, using randomly generated numbers produced by a blinded statistician. Thus, for example, departments in public hospitals nevertheless will have the same likelihood of initiating interventions at any particular step of the trial. A minimization procedure will be used to ensure that there is an equilibrium between an intervention and an observation phase based on several variables: baseline cesarean section rates, region of Greece, and unit size (annual number of births). Minimization has the advantage of matching small numbers of similar units which are analogous in certain unit characteristics [34, 35].

The totality of participating units will be entering the study simultaneously. An independent data center (Women’s Health Research Institute, University of British Columbia, Department of Obstetrics & Gynecology, Vancouver, Canada) will carry out the analysis of the baseline data as well as the allocation procedure and they will communicate their results to HSOG in Greece. This means that there will be a clear-cut distinction between study coordinators and generator of the intervention allocation [36]. All data and the results of the intervention, which latter will be analyzed in several steps, will be available at any time. Additional data relating to the puerperium period will be collected from women.

### Data

The ideal goal is to accumulate 20,000–25,000 deliveries, the sample size having been estimated based upon hospital birth rates for the year 2019. Based on these data, an assumed 57% cesarean rate (also from 2019 data) across centers, an intracluster correlation (ICC) of 0.3, a negligible secular trend, and a significance level of 0.05, we have > 99% power to detect an 8% absolute reduction in cesarean section rates (OR = 0.72). This calculation is based on the method of Hussey and Hughes, which assumes equal cluster sizes. Given that in this trial there is a large variation in the number of deliveries per hospital this assumption may be violated. To ensure the estimated power is robust to this and across possible randomization sequences, we carried out a simulation study. The parameters for the simulation were the same as those above, other than allowing for varying hospital sizes. The ICC was also varied to assess robustness to higher/lower values. In all scenarios, the available sample size resulted in >95% power. All simulations were conducted using R statistical software.

Intervention is the task of the obstetricians of the participating hospitals, but the analysis and conclusions will be derived from mothers and infants by calculating cesarean section rates and maternal and neonatal morbidity. While our intervention is aimed at introducing modifications and improvements within the national public and private health system, the evaluation will take place on both a local and a national basis.

The data will be collected after the completion of a cesarean section or a vaginal delivery by filling in the study questionnaires, one for the mother and the individual delivery and another for the final check of the newborn prior to discharge. The questionnaire data will be separately filled in for each birth in each maternity hospital during the observation or intervention period. The study questionnaire concerns (a) cesarean section indications, normal delivery, instrumental delivery, induction of labor, etc., and (b) data on maternal and neonatal morbidity and mortality. The questionnaires are uploaded to the trial’s website and they are based on the expected primary and secondary outcomes. A second questionnaire will be completed after contacting the mothers who participated in the study following their puerperium period (40 days or later). The obstetrician or a member of his/her team completes these questionnaires. A telephone call to the woman takes place by the study obstetrician and he/she fills the respective online questionnaires. The continuous data flow of new cases to the obstetricians is intended to assist and stimulate the obstetricians’ smooth transition to an updated mode of thinking and working. Moreover, standard questionnaires have been developed in order to minimize the additional tasks related to data collection carried out by the birth attendants in the course of the trial [37].

The main outcome of the study will be the change in the cesarean section rates and how effective the particular interventions are. The secondary outcomes of the study will be the maternal and neonatal morbidity that has occurred (Tables 6 and 7). The outcome variables will be the percentage of primary and secondary outcomes measured during the intervention period and the 2 months following the end of the intervention (rollout period). The amassed data will be employed in order to examine the potential for confounding of the intervention’s main effect on account of imbalances due to group randomization. There will be a clear separation of the data collection system for the determination of outcomes from the execution of the interventions. It will not be possible to blind the randomization due to the nature of the intervention; thus, data collectors will know whenever they are participating in the intervention. Finally, because the ability of participating hospitals to collect and review clinical data might possibly introduce bias into the outcome assessment, the data collection system will be, as far as possible, isolated from the intervention instruments to minimize the bias.

**Table 6 Tab6:** Maternal morbidity questionnaire: list of complications, diseases, and operations that will be included in the trial

**Maternal primary outcomes**	**Maternal secondary outcomes**
Manual removal of placenta	PPH (postpartum hemorrhage, secondary)
PPH (postpartum hemorrhage)	Removal of retained products (curettage, medicines)
Tachypnea /Bradypnea	Anemia
Oliguria that does not respond to fluids or diuretics	Blood transfusion
Inability to form clots (clotting disturbances)	Hysterectomy
Shock	Thrombosis/embolism
Cardiac arrest (absence of pulse and loss of consciousness)	Ileus
Cardiopulmonary resuscitation	Necrotizing enterocolitis
Severe acute thrombocytopenia (< 50,000 platelets/mL)	Fistulas
Red blood cell transfusions (≥ 5 units)	Wound dehiscence
ICU (intensive care unit) admission	Trauma infection
3^rd^ or 4^th^ degree perineal tear	Prolonged bladder catheterization
Uterine rupture	Urinary tract infection
Laparotomy (including hysterectomy)	Endometritis
Preeclampsia/eclampsia	Puerperal fever
Stroke	Sepsis
Uncontrolled convulsions/status epillepticus	Pelvic organ prolapse
Permanent neurological injury	Incontinence
Other	Puerperal psychiatric disorders

**Table 7 Tab7:** Neonatal morbidity, complications, and their monitoring

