The study does not include any interventions in the mothers or their fetuses and does not involve any pharmaceutical intervention or collection and handling of biological specimens. Instead, our study intervention applies only to the obstetricians and their labor ward practice. We will determine, among others, whether a cause of the increased cesarean section rates is a lack of compliance with current guidelines on labor management or the obstetricians’ tendency to favor a date and time convenient type of surgical labor management. In either case, obstetricians’ adherence to guidelines and follow-up tools for surgical management of labor is also expected to reduce the number of unnecessary cesarean sections or misguided interventions that can lead to cesarean section and change the doctor’s approach to vaginal birth.

The stepped-wedge cluster randomized trial comprises a novel research study design composed of the sequential transition of clusters (units) from control (observation) to intervention in a randomized order, until all clusters (units) have been revealed [27–30]. In current practice, this modality is increasingly being used for the evaluation of interventions. It will also reduce all practical and financial constraints to the minimum. Furthermore, there will be an effort to ensure that all enrolled maternity care professionals working in the selected units will comply with the intervention.

Specifically, there will be a period of monitoring and recording the activities of the maternity care unit with regard to the vaginal births and the cesarean sections (routine recording). During this period, professionals will continue with their usual in-service activities. The study will begin simultaneously in all maternity units, with a minimum recording period of routine activity for 8 months. During this period, the maternal and perinatal outcomes in each unit will also be recorded in detail via completion of questionnaires. The observation and intervention period durations will vary among the units although all units will enter the study at the same time; the intervention will be initiated in a different month (step wedged) for each of them. All the units will conclude the study at the same time, 28 months later.

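### The article claims outcome collection is clearly separate from the intervention, but the targeted obstetricians and their teams record the outcomes on the platform that delivers the feedback

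*Protocol article*

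**What the plan says.** The Data section states the safeguard without qualification: "There will be a clear separation of the data collection system for the determination of outcomes from the execution of the interventions". The same paragraph then concedes that the people collecting data will know when they are in the intervention. It names possible bias in outcome assessment and ends with a weaker promise: "the data collection system will be, as far as possible, isolated from the intervention instruments to minimize the bias".

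Other parts of the article say who does what:

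- **Target of the intervention** (Study design): "our study intervention applies only to the obstetricians and their labor ward practice". The Interventions section adds directors, trainees and midwives.
- **Consent** (Study design, text after Table 1): taken by the enrolled obstetricians who care for the woman.
- **Questionnaires** (Data): "The obstetrician or a member of his/her team completes these questionnaires".
- **Follow-up after the puerperium** (Data): "A telephone call to the woman takes place by the study obstetrician and he/she fills the respective online questionnaires".
- **Entry** (Data): all participating professionals insert their own data in REDCap.
- **Audit and feedback** (Table 3): "Live real-time statistics will be available for each participating department on the REDCap platform". Item 8 of the Interventions list expects this feedback to improve adherence.
- **Robson classification** (Interventions, item 7): an intervention component built into the electronic questionnaire.
- **Purpose of the data flow** (Data): "The continuous data flow of new cases to the obstetricians is intended to assist and stimulate" the obstetricians' move to a new way of working.

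**The concern.** A reader who relies on the separation sentence will think that the outcomes are shielded from the people whose behavior the trial tries to change. In fact the same people and the same platform serve both purposes.

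Two routes to bias remain open. First, the primary rate can move even if every entered record is correct, provided that consent or entry of cesarean births is less complete after crossover than before. The Study design section says staff will be told that implementation is monitored and evaluated, so a motive for such a difference exists. Second, many morbidity items depend on judgement or on the woman's own report (incontinence and puerperal psychiatric disorders, for example), and she gives that report to a study obstetrician. Morbidity is the trial's evidence on harm, and bias toward reporting no harm would be hard to see afterward.

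**Working it through.** **1. Claim against design.** Separation would require that outcome recording be done by people, or on an instrument, outside the intervention. The article places consent, questionnaires, the call and data entry with the targeted obstetricians or their teams, and it places feedback and Robson coding on the entry platform and form. The only organizational separation it describes is in the Randomization section, where an independent center handles allocation and the baseline analysis. That separates allocation from the coordinators. It does not separate outcome recording from the intervention.

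**2. The plan's own figures.** Inputs from the article: 22 units, two crossing per month for 11 months after 8 observation months, 26 months of births, 20,000–25,000 births, 57% against 49%, ICC 0.3, alpha 0.05 (two-sided assumed).

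OR = (0.49/0.51)/(0.57/0.43) = 0.725, which agrees with the stated 0.72.

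Hussey–Hughes variance with equal clusters:

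Var = I·s²(s² + T·τ²) / [(I·U − W)s² + (U² + I·T·U − T·W − I·V)τ²]

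Here I = 22 and T = 26. U = 2×(18+17+…+8) = 286, W = 5,412 is the sum of squared monthly totals, and V = 3,938 is the sum of squared unit totals. Births per unit-month are m = N/572, and p(1−p) = 0.57×0.43 = 0.2451. The article does not say how the ICC is defined, so two conventions were used:

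- A (ICC as a share of the total variance): τ² = 0.3×0.2451 = 0.0735, s² = 0.7×0.2451/m.
- B (0.2451 as the within-unit variance): τ² = (0.3/0.7)×0.2451 = 0.1050, s² = 0.2451/m.

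| Births | Convention | SE (points) | Power for 8 points |
|---|---|---|---|
| 20,000 | A | 1.25 | >99.9% |
| 20,000 | B | 1.49 | >99.9% |
| 25,000 | A | 1.12 | >99.9% |
| 25,000 | B | 1.33 | >99.9% |

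The stated power above 99% is reproduced. Power of this size gives no protection against bias.

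**3. Illustration of selective loss.** Let f be the share of intervention-phase cesareans that are not consented or not entered. The values of f are assumptions; the article gives none. With a true rate of 57% in both phases:

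recorded rate = 0.57(1−f) / [0.57(1−f) + 0.43], and the apparent OR equals 1−f.

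| f | Recorded rate | Change (points) | Apparent OR |
|---|---|---|---|
| 5% | 0.5415/0.9715 = 55.7% | −1.3 | 0.95 |
| 10% | 0.5130/0.9430 = 54.4% | −2.6 | 0.90 |
| 20% | 0.4560/0.8860 = 51.5% | −5.5 | 0.80 |
| 27.5% | 0.41325/0.84325 = 49.0% | −8.0 | 0.725 |

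**4. Scale against sampling error.** Across the four settings 1.96×SE runs from 2.19 to 2.92 points. Solving the formula in step 3 for those values gives f of about 8.5% to 11%. At that f the expected estimate only sits on the significance boundary, so p < 0.05 would occur about half the time.

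**The case against.** The strongest reply is that the defect is one sentence. The Data section openly admits the lack of blinding and qualifies the isolation of the system, so nothing is concealed. This stands, and it limits the point to the unqualified claim and to reliance on it.

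The reply continues that a cesarean is hard to misrecord, that the article calls for a form for each birth, and that it excludes only those unwilling to take part. A reader might infer that obstetricians freely choose which births to enter. The article does not say so. The documented route for selection is consent, with incomplete entry as a further possibility.

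The same staff use the same forms in both phases, and real-time access to birth data is not clearly confined to the intervention phase. Loss that is equal across phases would leave the comparison essentially unbiased. This also stands: a phase difference is plausible because feedback is an intervention component, but its size is unknown.

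The independent allocation center and the rule that site investigators do not see the full dataset (Data Availability) are real protections, though not of outcome recording. Finally, the article condenses a fuller protocol, so it cannot be inferred that checks against source records or registers are absent.

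**Conclusion.** The separation sentence is wrong as written: it credits the trial with a safeguard that its own description of data collection rules out. The exposure is phase-differential consent or entry for the primary outcome, and judgement-based or self-reported morbidity for the secondary outcomes.

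The size is illustrative. It rests on assumed omission shares confined to cesareans in the intervention phase, a true rate of 57% throughout, and a standard error of about 1.1–1.5 points from a formula with equal clusters, an assumption that the article itself says may be violated. On that basis roughly 8.5–11% omission brings the expected bias to 1.96 standard errors, and about 27.5% would be needed to imitate the planned effect.

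A reader might go further and infer that births are being withheld, or that a fall in the cesarean rate in this trial would be an artifact. The article supports neither. It shows that the stated protection is missing, not that bias has occurred.

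**What to change.** 1. Replace the separation sentence with a statement that unblinded staff in the intervened units record outcomes on the platform that also delivers feedback.
2. Compare monthly totals of births and cesareans entered for participating obstetricians with the unit's delivery register, at any remaining staff visits or retrospectively. Aggregate counts need no identifiers and so fit the anonymity rules in the Data section. Report capture by mode of delivery and phase.
3. Add one sensitivity analysis of the primary outcome on aggregate register counts, restricted to participating obstetricians where the register allows. Note that these counts include women who declined.
4. State that self-reported morbidity collected by the study obstetrician is open to reporting bias. Rest comparative morbidity conclusions mainly on verifiable items such as ICU or NICU admission, transfusion and laparotomy, and show the rest descriptively.

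The cost is some staff time, one extra analysis and fewer morbidity items that carry inference. Changing who makes the call is not part of this fix. The article assigns the call to the study obstetrician, so another caller would be a procedural change, and with recruitment due to end in October 2023 (Trial status) it would come too late for most women.
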